### Analyses

Analyses will follow an intent-to-treat approach, encompassing all eligible patients presenting before and after study participation at all sites. We anticipate an increase in the mean proportion of acute PE patients discharged without hospitalization from 12 to 25% across all sites.

### Primary outcome

To assess changes in the proportion of patients with acute PE discharged from the ED rather than admitted to the hospital, we will employ mixed-effects logistic regression to analyze the data. The dependent variable will be a patient-level measure of hospital discharge (binary yes/no). The primary independent variables will be a measure of pre-post implementation state, a time variable, and a categorical variable of the group assignment. We will include an interaction between the categorical group assignment variable and the pre-post implementation state variable. Fixed effects covariates will include key patient characteristics (e.g., age, sex, race/ethnicity, insurance status, comorbidity score) and random effects for the site. Individual sites will be included as a random effects variable in the model. In the primary analysis, we will exclude the 6-month implementation period in order to best compare pre- vs. post-implementations states. In an exploratory analysis, we will include a 3-phase analysis of the pre-implementation, active implementation, and post-implementation phases.

In a secondary analysis, we will also include data from non-participating control sites. These sites will be assigned to the pre-intervention state during the entire time period. Any site that does not care for adult patients (e.g., pediatric hospital) or patients with acute PE (e.g., psychiatric hospital) will be excluded from this analysis.

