### Adoption (primary outcome)

Our primary outcome will measure the change in the proportion of all acute PE patients discharged from the ED without hospitalization post-implementation vs. pre-implementation.

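### The primary model's group-by-state interaction gives four group-specific effects, but the plan defines and powers one overall change and does not say which quantity is the primary result

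*Protocol article*

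**What the plan says.** In the protocol article, Adoption (primary outcome) defines a single quantity: the "change in the proportion of all acute PE patients discharged from the ED without hospitalization post-implementation vs. pre-implementation". The opening of Analyses gives the hypothesis in the same terms: "We anticipate an increase in the mean proportion of acute PE patients discharged without hospitalization from 12 to 25% across all sites". Sample size and power claims more than 99% power for that increase, with about 580 acute PE patients per site.

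Primary outcome (under Analyses) then sets out a mixed-effects logistic model. Its main terms are: "The primary independent variables will be a measure of pre-post implementation state, a time variable, and a categorical variable of the group assignment". It adds: "We will include an interaction between the categorical group assignment variable and the pre-post implementation state variable". Site is the random effect ("Individual sites will be included as a random effects variable in the model"), and the active implementation months are left out ("In the primary analysis, we will exclude the 6-month implementation period in order to best compare pre- vs. post-implementations states").

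The interaction is not labelled secondary or exploratory. The same section does use those labels for other analyses: the three-phase analysis is exploratory and the one adding non-participating sites is secondary. Fidelity-informed Adoption repeats the primary adoption analysis, so it inherits the term.

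**The concern.** With four groups and a group-by-state interaction, no single parameter of the model automatically equals the overall change. Four group-specific changes exist, and an overall figure appears only once someone chooses how to combine them or which coefficient to read. The protocol makes no such choice, although it defines and powers one overall effect.

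Different effects by group are plausible here. Randomization says the groups were built around interdependencies such as a shared health system or EHR, and that rollout could not be stratified on baseline data. Each group also has one start date, so the group contrast carries site mix together with rollout order and length of follow-up.

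At stake is the headline result. Left open, the choice among several odds ratios from one fitted model could be made after the data are seen, and the stated power need not apply to the one reported.

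**Working it through.** **Inputs from the protocol.** 12 sites in 4 groups of 3; about 580 patients per site; 12% before and 25% after; a 3-month pre-implementation phase, 6 months of implementation (excluded), 12 months post-implementation, then maintenance of 12 months (Group 1) down to 3 months (Group 4).

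**Timeline.** Group 1: 3 + 6 + 12 + 12 = 33 months, or 11 quarters. Group 4: 33 − 3 − 12 − 6 = 12 months before implementation. The groups therefore step at 3-month intervals.

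**Assumed, not in the protocol.** Patients spread evenly (580/11 = 52.7 per site-quarter), two-sided alpha 0.05, and pre data running from the start of the timeline to each group's implementation. The form of the time variable is not given, so linear and calendar-quarter forms are both shown. Intracluster correlations of 0.01, 0.02 and 0.05 gave the same results.

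**Effect.** OR = (0.25/0.75)/(0.12/0.88) = 2.44; log OR = 0.894. Power = Φ(0.894/SE − 1.96).

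**Step 1: the plan's own figure.** A two-proportion comparison on 12 × 580 = 6,960 patients, with 20% to 50% of them in the pre state, gives power of about 1.00. Generalised least squares on site-quarter log-odds with one common state effect, linear time and maintenance data gives SE 0.147, so 0.894/0.147 − 1.96 = 4.12 and power is >0.999. Without maintenance data it is 0.983. The >99% is thus reproduced for one common effect, given linear time and maintenance data.

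**Step 2: the same layout with the interaction.** A hand check for Group 1 without a time term: pre patients 3 × 52.7 = 158, post patients 3 × 8 × 52.7 = 1,265. The variance is 1/(158 × 0.12 × 0.88) + 1/(1,265 × 0.25 × 0.75) = 0.0599 + 0.0042 = 0.0641, so SE = 0.253, matching the fitted value. With a time term and maintenance data:

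| Quantity | SE, linear time | Power | SE, calendar quarters | Power |
|---|---|---|---|---|
| Group 1 | 0.279 | 0.89 | 0.434 | 0.54 |
| Group 2 | 0.221 | 0.98 | 0.398 | 0.61 |
| Group 3 | 0.199 | 0.99 | 0.380 | 0.65 |
| Group 4 | 0.189 | >0.99 | 0.325 | 0.78 |
| Equal-weight average of the four | 0.152 | >0.999 | 0.343 | 0.74 |
| Common effect, no interaction | 0.147 | >0.999 | 0.323 | 0.79 |

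Group 1 is weakest because it has only one pre quarter.

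**Step 3: how far the reported figure can move.** Take assumed post rates of 18%, 25%, 27% and 30% in Groups 1 to 4, from 12% in each. The group odds ratios are (0.18/0.82)/(0.12/0.88) = 1.61, and likewise 2.44, 2.71 and 3.14. A logistic fit to the expected counts returns exactly these as the state odds ratio, depending only on which group is the reference. Sum-to-zero coding returns 2.41, and the model without the interaction returns 2.66.

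**Step 4: testing all four.** Four independent tests at 0.05 give a familywise error of 1 − 0.95^4 = 0.185.

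**The case against.** The strongest reply is that the target is clear even if the model sentence is not. The protocol names an overall mean change across all sites, an averaged or standardised contrast from this model delivers it, and the choice of contrast is detail that an article may leave to an analysis plan not shown here. Letting the effect vary is also defensible, given non-randomly formed groups and site-tailored pathways.

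Much of this stands. An overall answer can be derived from the model, and deriving it costs little power. It does not remove the point, because the mismatch is in what the article states: a primary model with four effects beside an outcome and a power claim for one.

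Three stronger readings are tempting but not supported.

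- **That the reported coefficient will belong to one reference group.** This needs reference coding and a decision to report the raw state coefficient. The protocol states neither.
- **That the interaction itself destroys the power.** The last two rows of the table show otherwise. With calendar quarters even the common effect reaches only 0.79, so most of that shortfall comes from the time term.
- **That the effects for Groups 1 to 3 cannot be estimated.** That needs pre data cut to each group's own 3-month phase and also calendar-quarter effects. The form of time is not stated, and Analyses includes all eligible patients before and after participation. Dropping the interaction would not cure it: under that cut the common effect has the Group 4 standard error, 0.325.

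**Conclusion.** The point holds as a mismatch between the primary model and the quantity it is meant to estimate. The protocol defines, hypothesises and powers one overall change, specifies a primary model with four group-specific changes, and designates none of them, nor any combination, as the primary result.

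This follows from the text alone. Its size depends on what is read off the model. Under reference coding with Group 1 as reference, power is about 89% (linear time) or 54% (calendar quarters), not over 99%. With linear time, Groups 3 and 4 would still exceed 99%. Under a named equal-weight average almost nothing is lost. The power figures rest on the even 11-quarter layout with 580 per site, and the odds ratios in Step 3 on invented post rates; they show sensitivity and are not forecasts.

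**What to change.** Settle this in the primary analysis text before outcome data are analysed. Either of two forms will do.

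1. **Preferred.** Fit the primary model without the interaction. Report one odds ratio with its p-value and the model-standardised risk difference over all 12 sites. Move group by state to a pre-specified exploratory heterogeneity analysis.
2. **Alternative.** Keep the interaction and name one averaged contrast, with its weights and scale, as the sole primary test.

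The first form assumes a common effect across groups, which the exploratory interaction analysis then checks. The second avoids that assumption at a small price: SE 0.152 against 0.147 with linear time, or power 0.74 against 0.79 with calendar quarters. Either is a sentence or two and needs no new data. Fidelity-informed Adoption should follow the same choice, since it repeats the primary model.

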#### Patient safety outcomes

These will be assessed among all patients with acute PE managed without hospitalization. Specifically, we will report the percent of patients who experience (1) return to the ED, (2) any bleeding that leads to healthcare system interaction, or (3) all-cause death within 30 days of the ED visit. A Data Safety and Monitoring Board will review safety data throughout the trial.

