**Methods/design:**

The study uses a cluster-randomized stepped wedge trial design to investigate a set of implementation strategies to support establishing low-risk PE pathways in 12 EDs. Clusters of three hospitals were randomly assigned to one of four start dates, staggered over a 12-month period. During an initial three-month pre-implementation period, we will work with site champions to identify key site personnel and understand site barriers and facilitators. We will then tailor the care pathway to local needs and capabilities. During the six-month active implementation period, we will provide coaching to help sites implement a multi-component intervention informed by behavioral economics intended to address multi-level (site, provider, patient) barriers and integrate the new care pathway for discharging low-risk PE patients. Sites are then followed for a minimum of 12 months post-implementation. Our primary aim is to assess the change in discharge rates of patients with acute PE pre- and post-implementation. Secondary and exploratory aims will assess change in patient safety outcomes along with other key implementation outcomes guided by the RE-AIM framework.

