A key barrier that has not been thoroughly considered is that ED clinicians commonly rely on fast-thinking (type I) heuristics to make rapid clinical assessment and treatment decisions. This is a necessary skill developed during training that allows ED clinicians to assess and treat critically ill patients rapidly. That same fast-thinking heuristic also maximizes their efficiency when caring for a large volume of patients with a wide range of clinical conditions. However, this fast-thinking heuristic can also impede the adoption of new evidence-based clinical practices (e.g., outpatient management of low-risk acute PE). Furthermore, a fast-thinking heuristic may constitute an important “blind spot” in the design of implementation strategies, as stakeholders are less likely to recognize or emphasize this heuristic’s contribution to decision-making as compared with other key barriers. As such, one crucial barrier to changing ED clinician behavior to improve discharge rates for low-risk PE patients is the need to alter ED clinicians’ well-established heuristic that associates an acute PE diagnosis with the need for hospital admission. Therefore, implementation strategies derived from behavioral economics (like pre-commitment, which asks clinicians to commit to following evidence-based practice, and point-of-care nudges, which provide just-in-time reminders when patients who can benefit from new practices or care pathways present) are promising implementation strategies to facilitate behavior change in the face of these ED clinician heuristics.

This study aims to test the implementation outcomes of a four-component intervention across twelve diverse EDs in the state of Michigan. We will evaluate the implementation of the care pathways to better understand the necessary components and test a strategy for scaling up pathway implementation, and also assess key safety outcomes to provide further evidence in support of outpatient management for patients with low-risk acute PE.

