### Effectiveness/Patient Safety (exploratory outcomes)

As well-implemented care pathways that discharge appropriate PE patients should be just as safe, if not safer, than care pathways that admit PE patients, effectiveness of the care pathway will be assessed through an examination of three patient safety outcomes, all assessed at 30 days post-discharge: (1) return to the ED, (2) any bleeding that leads to health care system interaction, and (3) all-cause death.

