Our study has important limitations. First, while our study includes 12 diverse hospital EDs across the state of Michigan, these sites may not represent the entire diversity of all hospital EDs in the US. Furthermore, practice variation from state-to-state and between the US and other countries may limit the generalizability of these findings. Second, data collection will rely on the existing MEDIC collaborative data registry. While this data is audited for accuracy and completeness, it does not have robust post-ED data included. Our safety analysis will focus on 30-day events using a data matching protocol with Medicare, Medicaid, and private insurer claims data when available. However, not all patients will have complete post-ED claims for these analyses.

In conclusion, innovative implementation strategies are needed to change ED clinician behavior and increase the use of evidence-based, guideline-recommended outpatient management of low-risk acute PE. This stepped-wedge trial will evaluate a four component intervention across 12 diverse hospital EDs participating in the MEDIC quality collaborative. If found to be effective and broadly adopted, this multi-component implementation program will provide a framework for nation-wide adoption of this high-value, evidence-based practice in the United States.

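### The 30-day safety outcomes are summarised only in patients sent home, a group the intervention itself reshapes, so the planned percentages cannot measure the change in safety that the abstract promises

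*Protocol article*

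**What the plan says.** All references are to the protocol article.

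- **Aim.** The abstract (Methods/design) states: "Secondary and exploratory aims will assess change in patient safety outcomes along with other key implementation outcomes". The Background says the trial will "assess key safety outcomes to provide further evidence in support of outpatient management".
- **Rationale.** The Effectiveness/Patient Safety section labels the outcomes exploratory. It introduces them by saying that well-implemented discharge pathways "should be just as safe, if not safer, than care pathways that admit PE patients". The three outcomes are return to the ED, bleeding that leads to contact with the health care system, and all-cause death.
- **Analysis.** The Patient safety outcomes section fixes the population: "These will be assessed among all patients with acute PE managed without hospitalization". It fixes the summary as follows: "we will report the percent of patients who experience" each event. It names no contrast.
- **General principle.** The Analyses section sets an intent-to-treat approach that takes in all eligible patients before and after participation, and expects discharge to rise from 12% to 25%.
- **Time origin.** The outcome definition reads "all assessed at 30 days post-discharge"; the analysis section reads "all-cause death within 30 days of the ED visit".
- **Data.** The limitations say that 30-day events come from claims matching and that "not all patients will have complete post-ED claims for these analyses".

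**The concern.** The aim is a change, but the analysis is a percentage in a subgroup. That subgroup is defined by disposition, which the intervention is designed to alter and which is the trial's primary outcome. Conditioning on it discards the before-and-after comparability that the stepped-wedge design and the intent-to-treat statement are meant to provide. Patients who move from admission to discharge appear in the safety denominator after implementation but not before.

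A higher percentage after implementation could therefore be read as harm when the discharged group has merely broadened. A stable or low percentage could be read as reassurance without showing what would have happened under the earlier practice. In a trial that deliberately moves patients out of hospital, these are the figures readers will look to for safety.

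**Working it through.** The article gives no safety event rate and no safety-specific power figure, so there is no planned figure to reproduce. The check uses its discharge proportions and labelled assumptions.

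**Inputs from the article:** discharge 12% before and 25% after (Analyses); about 580 acute PE patients at each of 12 sites (Sample size and power), so 580 × 12 = 6,960.

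**Assumed:** case mix is stable; patients who would have been discharged before still are; the event risks below; 30% of patients in the pre state; no clustering.

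**Step 1. Who is in the post-period denominator.** Share newly discharged = (25 − 12)/25 = 13/25 = 52%. The other 12/25 = 48% would have been discharged anyway.

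**Step 2. What the discharged-only percentage does when nobody's risk changes.** Let *a* be the 30-day risk in always-discharged patients and *b* the risk in newly discharged patients, each the same at home or in hospital. The pre percentage is *a*. The post percentage is 0.48*a* + 0.52*b*. The artefact is 0.52(*b* − *a*).

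| *a* | *b* | Pre | Post |
|---|---|---|---|
| 1% | 0.5% | 1.0% | 0.74% |
| 1% | 1% | 1.0% | 1.00% |
| 1% | 2% | 1.0% | 1.52% |
| 1% | 3% | 1.0% | 2.04% |
| 2% | 5% | 2.0% | 3.56% |

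The sign follows *b* − *a*, which the article does not give. In every row the rate in all acute PE patients is unchanged, because membership of that group does not depend on disposition. The same holds for PESI class I-II patients, who are classified by risk and not by where they are managed.

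**Step 3. What precision is available.** With 30% in the pre state:

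- all acute PE: 0.30 × 6,960 = 2,088 pre and 4,872 post;
- discharged only: 2,088 × 0.12 ≈ 251 pre and 4,872 × 0.25 = 1,218 post.

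The 95% half-width of a pre/post difference is 1.96 × √[p(1 − p)(1/n₁ + 1/n₂)]. At p = 2% this is about 1.9 points for discharged only and 0.7 points for all acute PE. Clustering, adjustment for time and exclusion of the implementation period would widen both.

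**Step 4. How far the all-PE contrast dilutes harm.** Only 13 in 100 patients change disposition. If discharge doubled their risk from 3% to 6%, the all-PE rate would move by 0.13 × 3 = 0.39 points, which is inside the 0.7-point half-width. PESI class I-II is the less diluted population, but the article does not give its size.

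**The case against.** The case on the other side is substantial and limits how far the point goes.

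- **Status.** Safety is exploratory in a hybrid type III implementation trial. A Data Safety and Monitoring Board reviews the data, and the primary inference is untouched. This stands and lowers the severity.
- **Comparison with admission.** A reader might infer that the trial commits to showing discharge as safe as admission and then omits the admitted arm. The documents do not support that. The sentence about pathways that admit is a rationale for choosing the outcomes; it states no test and no margin.
- **No contrast at all.** The article does not rule out showing the percentages pre and post, and the model for an exploratory outcome may sit in an analysis plan that is not shown. That stands, but the discharged-only population is stated outright, and a pre/post split does not cure it (Step 2).
- **Time origin.** A reader might infer that in-hospital deaths are dropped. In the stated population nobody is admitted, so the ED visit and discharge nearly coincide. The mismatch matters only once admitted patients are included.
- **Claims.** A reader might infer that events will be undercounted. That requires unlinked patients to be counted as event-free, which the article nowhere says; it discloses incomplete claims as a limitation.
- **Size.** The pathway targets low-risk patients, so newly discharged patients may carry no extra risk. Hence the range in Step 2 and not a single figure.
- **Remedy.** The all-PE contrast is itself insensitive (Step 4). Event rates in patients sent home remain a legitimate description.

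**Conclusion.** The point holds as a mismatch between aim and analysis. A percentage restricted to discharged patients, whether or not it is split by period, cannot measure the change in safety that the abstract announces, and it departs from the all-eligible-patients principle in the Analyses section. At the article's own 12% to 25%, about 52% of post-period discharged patients would be newly discharged, given stable case mix and continued discharge of those discharged before. The resulting artefact is 0.52(*b* − *a*): zero if risks are equal, reversed if newly discharged patients are at lower risk, and about one percentage point under the assumed 3% against 1%.

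It would go too far to say that the trial's data cannot address safety. The limit lies in the planned analysis, since the registry holds patients with both dispositions. Severity is moderate: the outcomes are exploratory, but the published aim and the stated analysis should agree.

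**What to change.** 1. Add a post-versus-pre analysis of each 30-day safety outcome regardless of disposition, in PESI class I-II patients and in all acute PE patients, using the mixed-effects model of the Primary outcome section. Report estimates with confidence intervals and label them exploratory.
2. Keep the discharged-only percentages as a descriptive table, shown pre and post, with a note that the composition of the group is expected to change.
3. Use one time origin, the index ED visit, in both the outcome definition and the analysis section.
4. Report the share of patients with linked claims by period, and do not count unlinked patients as event-free. State that a linked-only denominator may itself be selective.

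**Cost.** Claims matching must extend to admitted patients; the article gives no basis for pricing this. The registry cohort, the PESI I-II definition and the model already exist. Precision will be limited, especially for death and for the diluted all-PE contrast, so the result should not be presented as proof of equal safety.

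**Alternative.** If wider matching is not feasible, reword the safety aim in the abstract and in the Effectiveness/Patient Safety section so that it promises only a description of event rates in discharged patients.
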